#### Aims

To determine carriage prevalence, density and resistance of non-typeable *H. influenzae, M. catarrhalis*, and *S. aureus*, over the vaccine eras.

#### Outcomes

Proportions positive for carriage, proportions resistant to common antimicrobials (particularly β-lactams and macrolides), categorical carriage density and co-colonization will be reported and analyzed as per the pneumococcal/OM analyses.

(iv) Serotype specific differences in nasopharyngeal carriage between children with acute OM and diagnoses of OM with effusion or healthy ears and the impact of increasing valency PCVs on serotype dynamics and other known predictors (risk factors).

#### Aims

In a subset of children (completed primary immunization series, aged 6 month to 5 years) from BIGDATA, with both a nasopharyngeal swab and an ear examination of the same day, describe the vaccine and non-vaccine serotype carriage, and impact of increasing valency PCVs on the serotypes associated with a diagnosis of AOM or no AOM.

#### Outcomes

Proportions of children (with 95%CIs) positive for pneumococci, serotype specific carriage, and vaccine and non-vaccine type carriage will be compared (chi-square) in children with and without AOM. Regression analyses will describe associations with modifiable risk factors, age and time as described above.

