The burden of ear disease in NT Aboriginal children starts in the first weeks of life, driven by early, dense colonization of the nasopharynx with common bacterial respiratory pathogens including *Streptococcus pneumoniae*, non-typeable *Haemophilus influenzae* and *Moraxella catarrhalis* (10). *S. pneumoniae* causes considerable morbidity and mortality worldwide due to its ability to cause a range of mucosal and invasive diseases (including otitis media, sinusitis, conjunctivitis, pneumonia, meningitis and bacteremia) (11). The current pneumococcal conjugate vaccines (PCV) confer protection against up to 13 common serotypes (of the 100 known serotypes) causing invasive pneumococcal disease (IPD). The decrease in nasopharyngeal (NP) carriage of vaccine types (VT) among vaccinees has reduced pneumococcal transmission and rates of IPD in non-vaccinated groups as a result of herd effects (12). Near elimination of NP carriage by vaccine serotypes has also left a niche for non-vaccine types (non-VTs). Most populations have reported NP carriage replacement with non-VTs, as was observed in remote dwelling Australian Aboriginal children (13). Whilst non-VT serotypes are less likely to cause IPD than VTs, they continue to cause mucosal pneumococcal infections (including OM and bronchitis). Higher valency PCV trials are currently in progress (including15PCV, PCV20, PHiD-CV11, PHiD-CV12) (14–16). Carriage serotype epidemiology is needed for selection of vaccines as benefits will be population specific and driven by local serotype distribution and dynamics.

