2003	Randomized controlled trial of surfactant vs ciprofloxacin or sofradex for resolving discharge in Indigenous children in a Tiwi community	L (1–4) RCT (1)	32 (100%) 8.3/7.9 [4.4–13.2] **years**	Ears NP ED	Spn Hi Pa
2003 PCV7	Cross sectional surveillance of OM and bacterial nasal carriage and antibiotic resistance in Indigenous children from 27 remote communities (13, 25, 33)	X Surv (27)	644 (100%) 18/18 [6-30]	NP ED	Spn Hi Mc
2003–2005	Double-blinded randomized controlled trial of azithromycin vs. amoxicillin for treatment of acute otitis media in 16 communities (25, 26, 35, 36, 40–43)	L (1-3) RCT (16)	320 (100%) 17.5/13 [6-72]	Ears NP ED	Spn Hi Mc
2003	Cross-sectional surveillance of bacterial nasal carriage and antibiotic resistance in children attending 18 urban childcare centers in Darwin and Alice Springs	X Surv (18)	303 (unknown%) 33.6/34 [2.6-66]	NP	Spn
2004	Cross-sectional surveillance of bacterial nasal carriage and antibiotic resistance in children attending 23 urban childcare centers in Darwin and Alice Springs (25)	X Surv (26)	473 (unknown%) 33.7/33.4 [3.7-83.8]	NP	Spn Hi Mc
2005	Cross sectional surveillance of OM and bacterial nasal carriage and antibiotic resistance in Indigenous children from 18 remote communities (13, 33)	X Surv (18)	819 (100%) 34/34 [0-72]	NP	Spn
2005	Cross-sectional surveillance of bacterial nasal carriage and antibiotic resistance in children attending 26 urban childcare centers in Darwin and Alice Springs	X Surv (23)	394 (11%) 35.5/36.4 [3.2-65.1]	NP	Spn
2006- 2011	PneuMum: A randomized controlled trial of pneumococcal polysaccharide vaccination for Aboriginal and Torres Strait Islander mothers to protect their babies from ear disease (44–49)	L (1-4) RCT (4)	225 (100%) birth	Ears NP ED	Spn Hi Mc Sa
2008-2013	A double blind placebo-controlled randomized clinical trial of the use of oral azithromycin in Aboriginal children between 6 months and 30 months of age presenting with asymptomatic acute otitis media without perforation	L (1-3) RCT (14)	149 (100%) 16.2/16.1 [5–30.7]	Ears NP ED	Spn Hi Mc Sa
2008–2011	High Nasopharyngeal Carriage of Non-Vaccine Serotypes in Western Australian Aboriginal People Following 10 Years of Pneumococcal Conjugate Vaccination (50)	X Surv (40)	1500 (100%) 0–101 **years**	NP ED	Spn Hi Mc Sa

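### Chi-square is named for every serotype-specific AOM comparison with no provision for rare serotypes; if AOM children are a small share, very small p-values for rare types are overstated

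*Protocol article*

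**What the plan says.** Under Research Questions and Hypotheses, analysis (iv), Outcomes, the article plans to report "Proportions of children (with 95%CIs) positive for pneumococci" and then states that "serotype specific carriage, and vaccine and non-vaccine type carriage will be compared (chi-square) in children with and without AOM". It adds that "Regression analyses will describe associations with modifiable risk factors, age and time as described above". Chi-square is the only test named for the two-group comparison, and it applies alike to overall carriage, to the vaccine and non-vaccine groups, and to each serotype.

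The Aims paragraph of the same analysis limits the sample to children with a swab and an ear examination on the same day, described as "completed primary immunization series, aged 6 month to 5 years". The size of that subset is not given. The Introduction puts the coverage of current vaccines at "up to 13 common serotypes (of the 100 known serotypes", so carriage may be spread over many types. The number of serotypes found in this dataset is not stated.

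**The concern.** Pearson's chi-square is a large-sample approximation. It suits overall carriage and the vaccine/non-vaccine split, where counts will be large. For a rare serotype the expected number of AOM carriers may be around 1 or less. If the AOM group is also much the smaller one, a single AOM carrier can then produce a very small p-value. The approximation fails worst in that far tail, which is where a serotype would stand out from the others.

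Rare and newly appearing types matter to this programme. The Introduction ties serotype carriage data to the choice of vaccine, and Future Directions aims at detecting emerging serotypes.

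**Working it through.** The article gives no sample size, AOM share, prevalence or alpha for this comparison, so it has no figure to reproduce. Group sizes and prevalences below are assumptions, anchored to Table 2 where possible.

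**1. Plausible AOM numbers.** Three Table 2 studies recruited on an AOM diagnosis and list both ear examinations and NP swabs: 320 (2003–2005 trial), 149 (2008–2013 trial) and 31 (2000 cohort), so 320 + 149 + 31 = 500. This is before the age and immunization limits, and before adding AOM cases found in other studies. The predominantly young-child studies listing both procedures sum to 3,767 children, also before restriction. 500/3,767 = 13%.

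**2. Expected counts.** Expected AOM carriers = n(AOM) × serotype prevalence. Reaching 5 needs a prevalence of 5/149 = 3.4%, 5/320 = 1.6% or 5/500 = 1.0%. Rarer types fall short.

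**3. Single tables.** For 1/60 against 0/900, N = 960 and the uncorrected statistic is 960 × (1×900 − 0×59)² / (60 × 900 × 1 × 959) = 15.0, giving p = 0.0001. Exactly, the one carrier falls in the AOM group with probability 60/960 = 0.0625. That is the Fisher p, and half of it, 0.031, is the mid-P.

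| Carriers, AOM vs no AOM | Chi-square | Fisher | Mid-P |
|---|---|---|---|
| 1/60 vs 0/900 | 0.0001 | 0.063 | 0.031 |
| 1/60 vs 1/1,500 | 0.0007 | 0.075 | 0.038 |
| 2/60 vs 3/1,500 | 0.00003 | 0.014 | 0.007 |
| 2/100 vs 3/1,000 | 0.016 | 0.068 | 0.037 |

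In the first three rows mid-P is also far from chi-square, so Fisher's conservatism does not explain the gap.

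**4. True error rate.** With equal prevalence p in both groups, sum Bin(a; n1, p) × Bin(b; n2, p) over all tables whose uncorrected chi-square p-value is below alpha. The first two result columns give the range over prevalences of 0.1–2%. The last lists prevalences 0.1, 0.25, 0.5, 1 and 2% in that order.

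| AOM vs no AOM (AOM share) | Nominal 5% | Nominal 1% | Nominal 0.1% |
|---|---|---|---|
| 60 vs 1,500 (4%) | 4.3–7.3% | 1.6–4.7% | 3.32, 2.28, 1.22, 0.67, 0.48% |
| 149 vs 1,000 (13%) | 3.9–5.6% | 1.1–5.5% | 0.39, 0.60, 0.44, 0.31, 0.25% |
| 320 vs 2,000 (14%) | 4.1–6.1% | 1.0–1.8% | 0.69, 0.54, 0.35, 0.20, 0.16% |
| 500 vs 3,267 (13%) | 4.0–5.2% | 1.0–2.1% | 0.60, 0.36, 0.24, 0.19, 0.14% |
| 469 vs 1,500 (24%) | 2.3–4.9% | 0.3–0.9% | 0.04, 0.16, 0.18, 0.13, 0.12% |
| 300 vs 900 (25%) | 1.6–4.6% | 0.2–0.9% | 0.01, 0.10, 0.19, 0.17, 0.12% |

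Over a wider grid of 60–150 AOM against 900–1,500 no-AOM children, the rate at nominal 5% reached 8.3%.

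**5. Size of the p-value error.** Take null tables with chi-square p < 0.001 among 3,767 children, at prevalences of 0.1, 0.25, 0.5 and 1%. The median ratio of Fisher to chi-square p is 58, 14, 8 and 4.5 with 500 AOM children (expected counts 0.5, 1.25, 2.5 and 5). With a 20% AOM share it is 15, 7, 4 and 3, and with 30% it is 2 to 4 throughout. For tables just crossing p = 0.05 the ratio is mostly 1.5 to 3.

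**6. The alternatives.** Over the scenarios in step 4, mid-P stayed at or below nominal, within rounding, at all three levels. Fisher's true size at nominal 5% was 0.2–4.1%.

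**The case against.** The strongest reply is that the parenthetical chi-square is shorthand in a condensed article. It does not say uncorrected Pearson, and changing to an exact test in sparse cells is routine detail that a full plan could supply. This has weight and limits the point to a wording change. It does not remove it, because the article names one test for serotype-specific comparisons and nothing signals an exception.

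A continuity correction does rescue some tables: 1/60 against 0/900 becomes p = 0.07 and 1/60 against 1/1,500 becomes 0.12. It does not rescue all of them. For 2/60 against 3/1,500 the corrected statistic is 1,560 × (2,820 − 780)² / (60 × 1,500 × 5 × 1,555) = 9.28, p = 0.002, against a mid-P of 0.007.

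It is also fair that the aim is descriptive, that no alpha or rule for declaring a serotype AOM-associated is given, and that intervals accompany the proportions. A reader might infer that the analysis would name serotypes on one or two carriers; the article does not say so.

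A reader might also infer that most serotypes will have expected counts far below 5. The 100 is a count of known types, not of those in this dataset. With one serotype per child, at most n(AOM) × carriage / 5 types can reach an expected count of 5. If every child carries, 500 AOM children would allow 500/5 = 100 types, so a majority below 5 is certain only under about 250 AOM children.

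Last, Fisher is itself conservative and part of some quoted gaps is its own doing. That stands, and it favours mid-P.

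**Conclusion.** The point holds in a limited form. Chi-square is the stated test for serotype-specific carriage, and it can seriously overstate very small p-values when three conditions meet: an AOM share of about 15% or less, an expected AOM count of about 2 or less, and interest in p-values well below 0.05. The error in such p-values is then about 10-fold or more. The true error rate at nominal 0.001 is roughly 2 to 7 times nominal for AOM groups of 149 to 500, and up to about 33 times with 60. At 5% the test stays near or below nominal in most scenarios, and with an AOM share of about 25% the rate at nominal 0.001 is at most about twice nominal.

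That AOM children are the smaller group is itself an assumption. A general statement that the serotype p-values are wrong by one to two orders of magnitude is not supported: the article gives none of the inputs it needs, and the error depends strongly on AOM share and rarity. The overall and vaccine/non-vaccine comparisons are not affected.

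**What to change.** In the Outcomes paragraph of analysis (iv), state that serotype-specific comparisons use a mid-P exact test (or Fisher) whenever any expected count is below 5, with score or exact 95% intervals for those proportions. Keep chi-square for overall and vaccine/non-vaccine carriage. This adds to any handling of repeated swabs from the same child and does not replace it.

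The cost is one sentence and standard software. The downside is some conservatism at the 5% level for the rarest serotypes, more with Fisher than with mid-P. No particular form of regression is required.

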#### Outcomes

Presence of OM and different OM diagnoses (proportions with 95% CIs) will be reported, per time period and region. Markers of severity (size of perforation, volume of discharge, bilateral disease) will be compared over time and vaccine eras. Regression analyses, corrected for repeated measures in the same participants where relevant, will be used to describe OM associations with modifiable risk factors, age, time, prior antibiotic use, gender and geographic region.

Multilevel mixed effects models will be used, utilizing fixed effects for antibiotics, vaccination, age, gender and year; and random effects for region.

(ii) Impact of increasing valency PCVs (PCV7, PCV10 and PCV13) on nasopharyngeal carriage dynamics of pneumococcal serotypes, and associated antibiotic resistance, and by region and other known predictors (risk factors).

PCV impact on nasopharyngeal carriage has been addressed in specific EHRP study publications, as the vaccines have been introduced (Table 1). However, a comprehensive descriptive analysis including all study data from the non-vaccine studies and pre-vaccine era has not been undertaken.

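### Analysis (iv): the AOM versus no-AOM chi-square names no era or study stratum, so AOM status is partly confounded with vaccine era and enrolment design

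*Protocol article*

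**What the plan says.** All references are to the protocol article.

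- **Eligibility for (iv)** (Research Questions and Hypotheses, item (iv), Aims). Children aged 6 months to 5 years who have finished the primary vaccine course are eligible, "with both a nasopharyngeal swab and an ear examination of the same day". No study type is excluded. The aim also covers the "impact of increasing valency PCVs on the serotypes associated with a diagnosis of AOM or no AOM".
- **Comparison** (item (iv), Outcomes). Carriage proportions are given with 95% confidence intervals, and "vaccine and non-vaccine type carriage will be compared (chi-square) in children with and without AOM". The sentence names neither era nor study.
- **Regression** (item (iv), Outcomes). "Regression analyses will describe associations with modifiable risk factors, age and time as described above". The model this points back to is in item (i), Outcomes, "utilizing fixed effects for antibiotics, vaccination, age, gender and year; and random effects for region".
- **Contrast with (ii)** (item (ii), Outcomes). That analysis is limited to non-interventional data and compares by age, region and vaccine era.
- **Sources** (Table 2). One entry for 2003-2005 is "Double-blinded randomized controlled trial of azithromycin vs. amoxicillin for treatment of acute otitis media in 16 communities". The 2005 remote survey is titled "Cross sectional surveillance of OM and bacterial nasal carriage and antibiotic resistance in Indigenous children from 18 remote communities", but its procedures column lists only a nasopharyngeal (NP) swab. The 2003 remote survey has a similar title and lists NP and ear discharge swabs.

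**The concern.** The Introduction says that vaccine serotypes in carriage were replaced by non-vaccine types in this population, so calendar period affects which serotypes are found. If the AOM group is weighted towards one period and the no-AOM group towards another, a serotype common in the first period will look associated with AOM even if it has no such association within any period. A later replacement serotype will look protective.

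Data Limitations acknowledges that trial eligibility followed a specific OM diagnosis, so the imbalance would come from how children entered the dataset. The Introduction also says carriage serotype data are needed for choosing vaccines, so a spurious link between a serotype and AOM could matter in practice.

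**Working it through.** The article states no sample size, AOM count or era date for (iv), so there is no planned figure to reproduce. The check tallies Table 2 and then asks what a pooled test would show if AOM had no effect within a period.

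**Inputs from Table 2 (ears and NP both listed)**
- AOM-entry trials: 320 (2003-2005) and 149 (2008-2013).
- Remote surveys 2008-2013: 54 + 174 + 253 + 568 + 276 + 371 = 1,696.
- Urban survey 2010: 462.
- PCV7 carriage cohort 2001-2004: 97.
- Childcare hygiene trial 2001, not entered on AOM: 456.
- Not counted, because one procedure is not listed: remote surveys 2003 (644) and 2005 (819), and urban survey 2012 (607).

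**Assumptions, not in the document.** AOM prevalence is p = 10-40% in remote sources and u = 5-20% in urban sources not selected on AOM. There is one record per child. Carriage of a given serotype group is 15% early (to 2005) and 5% late (2008-2013), whatever the AOM status. The age and vaccination criteria could not be applied to the counts. Pre-2001 studies, the maternal vaccine trial and the infant vaccine trial are left out, because vaccination status or age at visits is unclear.

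**Formulas.** With early share s in a group, group carriage = 0.15s + 0.05(1 - s). The pooled odds ratio is the ratio of the two carriage odds. The true value is 1.

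**Remote studies only, all 97 cohort children counted as no AOM**
- AOM: early 320, late 149 + 1,696p.
- No AOM: early 97, late 1,696(1 - p).
- p = 10%: early shares 320/638.6 = 50.1% and 97/1,623.4 = 6.0%. Carriage 10.0% v 5.6%, odds ratio 1.88.
- p = 40%: early shares 320/1,147.4 = 27.9% and 97/1,114.6 = 8.7%. Carriage 7.8% v 5.9%, odds ratio 1.35.

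**Urban studies added, cohort split by p**
- AOM: early 320 + 97p + 456u, late 149 + 1,696p + 462u.
- No AOM: early 97(1 - p) + 456(1 - u), late 1,696(1 - p) + 462(1 - u).
- p = 20%, u = 10%: early shares 385.0/919.4 = 41.9% and 488.0/2,260.6 = 21.6%. Carriage 9.2% v 7.2%, odds ratio 1.31.
- Over the whole range, early shares are 31-51% (AOM) and 19-25% (no AOM), and the odds ratio is 1.08-1.50.

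**Other carriage values**

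| Carriage early / late | Remote only | With urban studies |
|---|---|---|
| 15% / 5% | 1.35-1.88 | 1.08-1.50 |
| 12% / 6% | 1.19-1.46 | 1.05-1.29 |
| 20% / 5% | 1.50-2.28 | 1.11-1.68 |

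**Period boundary.** The 2008 and 2009 surveys may belong to the PCV7 era. If early is extended to the end of 2009 and the 149-child trial is split in half, early shares are 41-65% (AOM) and 13-32% (no AOM), with or without the childcare trial. The imbalance remains.

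**If the 2003 and 2005 remote surveys did include ear examinations.** Adding 644 + 819 = 1,463 early children, split by p, to the tally with urban studies gives a 15%/5% odds ratio of 1.05-1.13.

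**If childcare visits rather than children are counted.** Table 1 gives 5,720 urban ear examinations. At one per child in the 2010 and 2012 surveys, 5,720 - 462 - 607 = 4,651 remain for the 2001 trial, about 10.2 per child. With p = 20%, u = 10% and all other sources at one record each:
- AOM early share: 804.5/1,338.9 = 60.1%.
- No-AOM early share: 4,263.5/6,036.1 = 70.6%.
- Odds ratio: about 0.90.

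If those visits qualify, even the direction of the bias could change.

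**The case against.** The article does not say that the chi-square is pooled across eras. The aim of (iv) includes vaccine impact on serotypes by AOM status, which suggests results by era, and exact stratification is often left to a full plan. Data Sources promises suitable inclusion criteria for each analysis. The planned regression contains year and vaccination. With year as categories, early AOM cases that lack concurrent comparators mainly cost precision and do not by themselves create a serotype association. Enrolling on AOM is a form of case sampling and not a fault in itself.

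Much of this stands. A reader might infer that the test simply compares vaccine periods. The document does not support that: the 2008-2013 surveys and the 149-child trial supply later AOM cases, and the cohort, the childcare trial and trial follow-up visits can supply early no-AOM records. A reader might also infer that a year term cannot help. It would remove part of the era confounding. Nor is it certain that the 2003 and 2005 surveys supply no comparators, because their titles and the procedures column disagree.

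What does not stand is that the text already settles the matter. Item (ii) states both safeguards, a non-interventional restriction and a breakdown by era. Item (iv) states neither for its comparison. The only eligibility criteria given for (iv) admit children from AOM-entry trials. The regression in (iv) is described for risk factors, age and time and not for the AOM contrast, and its only random effect is region. Nothing in it represents study or enrolment on AOM.

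**Conclusion.** The concern holds in a limited form. Carried out as worded, the AOM versus no-AOM chi-square is partly confounded by vaccine era and enrolment design. This follows from Table 2 and the eligibility wording and needs no assumed figure.

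The size cannot be fixed from the document. Under no true association, 15% versus 5% carriage by period and one record per child, the pooled odds ratio is about 1.1-1.5 with the urban studies and 1.35-1.88 with remote studies only. These figures rest on assumed AOM prevalence and carriage. They shrink if the 2003 and 2005 surveys had ear examinations, and the direction may change if repeated childcare visits count. The article does not say how many 2001 childcare children meet the vaccination criterion. The planned year and vaccination terms reduce the era part of the bias and leave the study and AOM-entry part.

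**What to change.** 1. In item (iv), Outcomes, make the main AOM versus no-AOM comparison stratified by vaccine era and study, by Mantel-Haenszel or by a regression with terms for AOM status, era and study.
2. Label the crude chi-square as descriptive.
3. Add a sensitivity analysis restricted to studies that did not enrol on an OM diagnosis. Removing the AOM-entry trials from the main contrast altogether is debatable and is better placed here.
4. Tabulate AOM and no-AOM records by study and era, and reconcile the titles and procedures entries of the 2003 and 2005 remote surveys in Table 2.

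The cost is plan wording and a routine stratified analysis. The downside is lower precision for the PCV7 era. A study stratum in which every record is AOM adds nothing to a within-study contrast, so the 320 + 149 = 469 AOM-entry children would contribute to it mainly through any follow-up visits without AOM.

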### Future Directions

Beyond these initial analyses, other projects are being proposed for these data. Building on the pneumococcal carriage analyses, we aim to develop an efficient remote community and childcare center sentinel surveillance model for pneumococcal serotypes to determine efficient surveillance methods to detect emerging pneumococcal serotypes and resistance, and to improve the efficiency of sampling (by age range, geographic region, and sampling frequency). Modeling methodology is yet to be finalized. Accuracy of surveillance models will be tested in cross-sectional prospective studies across the NT.

Where we have comprehensive monitoring of individual children, we intend to examine the relationship between persistent ear disease and hearing loss in infancy and early childhood with subsequent outcomes such as hearing aid use and ENT surgical procedures. We will also describe ongoing indicators of life trajectory by combining our data with government held administrative data through the SA-NT Government data-linkage program. Data will be analyzed using multivariate regression approach with appropriate link function. Multivariate regression will be fitted between ear diagnoses and education and health outcomes, using children with healthy ears as the reference. Linking Health and Education administrative datasets to BIGDATA will facilitate the long term follow up of children with persistent OM diagnoses. This would enable an assessment of the impact of current treatments on perforations, and whether specialist services including hospitalization, ear surgery for grommets and tympanoplasties, and availability of hearing augmentation impact AEDC (Australian Early Development Census) and NAPLAN (National Assessment Program—Literacy and Numeracy) results, school attendance, maltreatment and later engagement with the justice system.

A cascade analysis approach will be used to identify which forms of OM receive more appropriate management (e.g., antibiotic prescribing guidelines, follow-up schedule, correct prescribing, audiology and specialist referrals met) and any management trends over time. We will also describe the region and age that contribute to better outcomes, and the potential impacts of vaccine and antibiotic prescribing guidelines. These detailed data will be used to identify critical timepoints where disease progression might be halted or reversed, and critical age groups for maximizing the benefits of hearing aids or surgery on language development, social development, and education outcomes.

We anticipate that these analyses will further support policies and programs aimed at reducing disadvantage attributed to early childhood ear and hearing problems. The analyses will also identify priority gaps in knowledge and lead to improved design of future studies aimed at eliminating the contribution that ear and hearing problems make to poor quality of life.

